## Abstract

**Introduction:**

People with serious mental illness (SMI), which includes people with diagnoses of schizophrenia spectrum and bipolar disorders, face significant health inequality. This includes a life expectancy reduced by 15–20 years mostly due to premature cardiovascular disease (CVD) compared with the general population. Excess weight gain and related comorbidities are preventable risk factors for CVD. To improve the understanding and management of CVD in people with SMI, we will examine the association between SMI and: (1) weight change; (2) cardio-metabolic risk factors for CVD; and (3) incidence of and mortality from CVD. We will also (4) examine the incidence of referral to weight management services for people with SMI compared with people without SMI.

**Methods and analysis:**

In this retrospective cohort study, we will link general practice records from the UK Clinical Practice Research Datalink Aurum database. We will establish a cohort of patients diagnosed with SMI between 1998 and 2020 who are matched with up to four controls on age, sex, general practice and calendar year. We will use multivariable mixed-effects linear regression models and Cox proportional hazard models with sequential adjustment for potential confounders identified by separate directed acyclic graphs.

**Ethics and dissemination:**

This study has been reviewed and approved by the Independent Scientific Advisory Committee for Medicines and Healthcare products Regulatory Agency database research. The results will be published in a peer-reviewed journal.

Strengths and limitations of this studyThe key strengths of the study include the representative population contained in the Clinical Practice Research Datalink Aurum, the sizeable and linked dataset, and substantial statistical power.However, limitations include its observational nature and potential for residual confounding due to lack of information on some factors.There is also potential for selection bias since physical health checks are not always performed on random population samples.

## Introduction

Serious mental illness (SMI) includes psychotic disorders like schizophrenia spectrum and bipolar disorders, which are marked by hearing, seeing, or believing things that are not real.^1^ People with SMI have a life expectancy that is approximately 15–20 years lower than the general population.^2^ Two-thirds of premature mortality in this group is explained by preventable cardiovascular disease (CVD).^3^ A 2017 meta-analysis reported people with SMI have a significantly increased incidence of and mortality from than the general population: HR: 1.78, 95% CI 1.60, 1.98.^4^ This indicates an important clinical need to identify the factors underlying the higher incidence of CVD for this group and routes for prevention and treatment.^5 6^

Overweight (body mass index (BMI) 25–29.9 kg/m^2^) and obesity (BMI≥30 kg/m^2^) are causally linked to cardio-metabolic abnormalities like insulin resistance, dyslipidaemia and hypertension, which are major preventable risk factors for CVD. Latest figures show that 64% of adults in the UK are classified as overweight or obese.^7^ Overweight and obesity have not been consistently reported for people with SMI. A 2018 report based on a representative sample of English general practice records found that people with SMI were three times more likely to have obesity between the ages 15–34, and 1.6 times more likely for ages 55–74 compared with the general population.^8^ However, these estimates were limited by high rates on non-completion of BMI in general practice. Moreover, other estimates are often drawn from cross-sectional analyses and often include small numbers of people attending specific services within a geographical area with no comparison group.^4^

The factors underlying excess weight gain in people with SMI are multifactorial. Psychotropic drugs (ie, antipsychotics, antidepressants, mood stabilisers) are the mainstay treatment for the symptoms of psychosis and affect weight.^9^ Evidence from clinical trials has linked these drugs to rapid weight gain, but the long-term effects after a diagnosis are unclear.^9^ In one 11-year follow-up study of people with schizophrenia, increased CVD mortality was reported in people treated with quetiapine (adjusted HR: 1.41, 95% CI 1.09 to 1.82) and reduced CVD mortality in people treated with clozapine (adjusted HR: 0.74, 95% CI 0.60 to 0.91).^10^ However, these estimates may result from unmeasured confounding by socioeconomic and other demographic factors.^11^ Accordingly, a better understanding of the long-term impact of medication on weight change, cardio-metabolic risk factors, and incidence of and mortality from CVD is warranted.

Other factors that cause weight gain include unhelpful dietary patterns and physical inactivity. These behaviours are more common in people with SMI compared with the general population and may reflect the social disadvantage to which SMI contributes.^12^ In addition, the prevalence of smoking is estimated to be twice that in people with SMI compared with general population,^13^ and evidence shows people with schizophrenia smoke more cigarettes per day and more intensely than the general population of smokers.^14^ Other studies using polygenic risk scores for liability to schizophrenia have found no association between those scores and physical health outcomes except for conditions mediated through obesity and smoking.^15^ This suggests that the excess risk to people with SMI are modifiable.

Since obesity is modifiable, US and UK clinical guidelines recommend intervening to prevent and manage obesity. In the UK, the first-line intervention is general practitioner (GP) advice or a referral to a weight management programme to support an energy-restricted diet and increase physical activity for people with a BMI >25 kg/m^2^.^16 17^ In the general population, trials of such programmes lead to greater weight-loss than self-directed attempts.^18^ Another study in the general population reported the rates of referral between 2005 and 2012 was 20.0 (95% CI 19.3 to 20.8) per 1000 person-years, compared with weight-related advice at 30.3 (29.3 to 31.4).^19^ This rate is low, and although these interventions may not be recorded, other evidence also point to low rates of intervention.^20^ However, we have no data on whether GPs are using the annual review of people with SMI, which focuses specifically on preventative healthcare, to provide support for weight management such as referrals to weight management programme.

We have been unable to find studies that have followed people with SMI over several years to examine how weight and cardio-metabolic profiles change. It is possible these relate to ongoing psychotropic and/or weight management programmes. The longest study to date was an 18-month trial of people with schizophrenia. In this study, participants randomised to olanzapine had greater increases in weight, glycaemia and adverse lipid profile than other antipsychotics.^21^ Randomised controlled trials (RCTs) are often limited to short follow-up of selected populations, and there are methodological issues surrounding imputation strategies used to address high dropout rates.^22 23^ Thus, it remains unclear how much weight and cardio-metabolic profiles change over the longer term, and how much of the excess incidence and mortality from CVD is explained by those changes in people with SMI.

In this protocol, we outline our plans to address this gap in a large, retrospective, population-based study in people with SMI matched with controls without SMI in the UK from 1998 to 2020. Our objectives are to:

Examine the association between SMI and weight change.Examine the association between SMI and change in cardio-metabolic risk factors for CVD.Examine the association between SMI and incidence of and mortality from CVD.Compare incidence of advice and offer and actual referral to weight management services in people with both SMIs and BMI ≥25 kg/m^2^ with controls.

## Methods and analysis

### Patient and public involvement

We consulted 12 members of the public with lived experience of SMI to ensure the outcomes that matter to them are included in the protocol. Their continued involvement will inform the dissemination of our results.

### Design

This protocol is written according to the ‘REporting of studies Conducted using Observational Routinely-collected health Data’ statement.^24^ We will use a retrospective cohort using individual patient data from a large primary care database to examine all objectives. The planned study start date is 01 September 2021 and end date is 31 August 2024.

### Data source

We will use the Clinical Practice Research Datalink (CPRD) Aurum—a governmental, not-for-profit research service holding anonymised primary care records drawn from participating general (primary care) practices dating back to 1987 (http://www.cprd.com). To date, it encompasses routinely collected patient data records of around 16 million patients who are currently registered with some 700 participating general practices. Patient demographic data (ie, year of birth, sex and ethnicity), characteristics (ie, height, weight, smoking status), symptoms, clinical diagnoses, consultations, referrals, prescribed medications and results of investigations are available.

### Data linkage

Data will be linked to the Hospital Episode Statistics (HES) and the Office for National Statistics mortality databases. Data linkage to the practice level Index of Multiple Deprivation (IMD), as a proxy measure for socioeconomic status (SES), will also be used when describing the baseline characteristics in the descriptive analyses and in secondary analyses.

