#### Comparison group

The unexposed represents the counterfactual and will include patients without an SMI Read code ever (hereafter *unexposed*) drawn from the source population. Up to four unexposed matches will be selected at baseline only if they have a qualifying weight Read code within±one year of the index date to the exposed in which they are matched. The matching variables include: age, sex, practice and calendar time. All weight Read codes will be extracted.

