### Confounding

We have identified confounding variables using directed acyclic graphs (DAGs), which aims to theoretically formalise potential confounders, colliders and biasing relationships.^26^ The DAG for each objective is described in online supplemental material S1. The DAG for objective 1 shows one direct path from the exposure (ie, SMI) to the outcome (ie, weight change), and four indirect paths: via health behaviours (ie, alcohol use, smoking and diet), SES status, psychotropic medication, and healthcare access and provision. Diet and physical activity are latent variables in CPRD Aurum because they are unmeasured. There are three confounding paths: via age, sex and ethnicity.^27 28^ Thus, the minimally sufficient adjustment for the total effect of SMI status on weight is to adjust for age, sex, and ethnicity.

10.1136/bmjopen-2021-053427.supp1Supplementary data

Frequency matching will ensure our ability to adjust for confounding variables that include age, sex, and calendar year, and matching on practice will remove practice-specific variables. In addition, we will fully adjust our models by considering several covariates in the relationship between the exposure and outcome (see table 2). All categorical variables will be analysed using the natural reference category as the reference group. Data on individual prescriptions for psychotropic and cardio-metabolic medications will be extracted from the primary care data from index date until censoring. For psychotropic medications, drugs will be classified according to the British National Formulary. For objectives 2 and 3, we will assess the impact of weight gain on change in cardio-metabolic risk factors and incidence of CVD using mediation analysis to allow us to estimate the direct (unmediated) and indirect (mediated) effects of SMI on CVD risk and incidence. To do this, we will fit two regression models: one regressing the outcome on the exposure, adjusting for confounders and another regressing the mediator on the exposure and confounders using the Stata *Med4way* command to estimate mediated effects.^29^ For objective 4, we will assess the presence of confounding by comparing estimates with and without adjustment. We will use Read codes, which have been previously developed by our team, to identify outcome and covariate records.

**Table 2 T2:** Confounders

Confounders and covariates		Measures

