Health behaviours	Smoking status	Categorical (0=never; 1=ex-smoker; 2=current smoker (light: 1–9 cigarettes/day; moderate: 10–19 cigarettes/day; heavy: 20+ cigarettes/day)). This is coded in GP records. We will use the most recent recorded value of smoking status at the study start date.
	Alcohol use	Continuous (units per week). This is coded in GP records. We will use the most recent recorded value of alcohol use at the study start date.
Demographics	Socioeconomic status (SES)*	Categorical (quintiles)
	Ethnicity†	Categorical (white; Asian or Asian British; black or black British; other ethnic group, mixed)
	Sex†	Binary (0=male; 1=female)
	Age at study entry, in years	Continuous
Physical and/or medical factors	Baseline weight status (body mass index (BMI))	Categorical (normal weight (BMI 18.5–24.9 kg/m^2^); overweight (25.0–29.9); obese (30.0–34.9); severe obesity (35.0–35.9); morbid obesity (40.0–44.9)
	Psychotropic medication	Categorical (antipsychotics (first-generation and second-generation); antidepressants; mood stabilisers)
	Cardio-metabolic medication	Categorical (blood glucose lowering medications; antihypertensive treatments, statins)
We include the following additional variables for objectives 3 and 4 only		
CVD risk factors	Total cholesterol/HDL ratio	Continuous
	Systolic and diastolic blood pressure	Continuous
	Glycaemia	HbA1c/fasting blood glucose (FBG)

*This variable is grouped according to practice level Index of Multiple Deprivation. This is an indicator of material deprivation based on income; employment; health deprivation and disability; education, skills and training; crime; barriers to housing and services; and living environment. It is categorised as quintiles 1–5 with 1 being the most deprived and 5 being the least deprived.

†This variable is grouped according to recommendations by the UK Office for National Statistics.^33 34^

CVD, cardiovascular disease; GP, general practitioner; HbA1c, haemoglobin A1c; HDL, high-density lipoprotein.

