Since the study is descriptive, any association observed would not imply an SMI diagnosis is causative of adverse physical health outcomes. However, we might assume the greater the magnitude of the observed association the less likely it is due to bias and more likely due to a causal process.^32^ Furthermore, diet and physical activity are unmeasured confounders because they are unobserved in CPRD Aurum. Similarly, other unmeasured confounders like poverty may place people with SMI at increased risk of homelessness, which has consequences on healthcare access and provision. We address this potential confounding by linking to patient level IMD as a proxy measure of SES, but acknowledge this may not fully capture deprivation and leaves room for residual confounding. Moreover, information bias may be present since the CPRD Aurum relies on a GP recording of health outcomes. Furthermore, we can only examine primary care prescriptions. Any prescribing solely within secondary care may not be included as this was not historically routinely recorded in GP records. Thus, it is possible we will miss the first prescription(s). Finally, physical health checks are not always performed on random samples of the population, and it is possible that more regular testing is done on people with overweight and obesity. We expect that some patients will have incomplete information recorded. However, by determining what proportion of patients do not have appropriate information recorded, we can evaluate the scale of these problems, and highlight the need for improved recording for continuity of care between healthcare professionals.

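### SES is defined by practice-level IMD in a practice-matched cohort, so it cannot adjust for within-practice deprivation as the Discussion says patient-level IMD will

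*Protocol article*

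**What the plan says.** The article states the level of the deprivation index three times, and the statements disagree.

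- Protocol article, Data linkage: "Data linkage to the practice level Index of Multiple Deprivation (IMD), as a proxy measure for socioeconomic status (SES"). The same sentence gives its role: it "will also be used when describing the baseline characteristics in the descriptive analyses and in secondary analyses".
- Protocol article, Confounding, footnote to Table 2 on the SES covariate: "This variable is grouped according to practice level Index of Multiple Deprivation", in quintiles.
- Protocol article, Discussion, after naming poverty as an unmeasured confounder: "We address this potential confounding by linking to patient level IMD as a proxy measure of SES".

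The design matches on practice. Under Comparison group, "The matching variables include: age, sex, practice and calendar time", and "Up to four unexposed matches will be selected at baseline". The Confounding section adds that "matching on practice will remove practice-specific variables".

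The same section describes the objective 1 DAG. SES lies on one of "four indirect paths: via health behaviours (ie, alcohol use, smoking and diet), SES status, psychotropic medication" and healthcare access. The minimal adjustment set for the total effect is age, sex and ethnicity. The models are nevertheless to be fully adjusted using covariates from Table 2, which lists SES, and Primary analyses names SES among the exploratory interactions.

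**The concern.** The Methods and the Discussion describe different variables, and under this design the choice between them matters. An index attached to the practice is one of the practice-specific variables that the plan itself says matching removes. Listing it as an adjustment covariate adds nothing on the question that the Discussion raises, which is whether patients with SMI are poorer than their comparators.

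Three planned outputs depend on the answer:

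- The baseline table would compare SES between groups whose SES value is largely aligned by the matching, whatever the deprivation of the patients themselves.
- The fully adjusted and secondary models would appear to adjust for SES while leaving the within-practice difference in place.
- The SES interaction would concern the deprivation of the practice, not of the patient.

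The Discussion does admit residual confounding, but the caveat is attached to a patient-level proxy that the Methods do not plan.

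**Working it through.** **The plan's own figure.** The plan gives no figure on this point. Its one calculation, the minimum sample of 3907, can be reproduced: 3% versus 1.3 × 3% = 3.9%, two-sided alpha 0.05, 80% power, one exposed to four unexposed, gives 15,628 unexposed and 15,628 × 0.25 = 3907 exposed. It does not depend on the level of IMD. Only its relative risk of 1.3 is used below, as a yardstick.

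**Step 1: what a practice-level covariate can carry.** Write the deprivation of patient *i* in practice *j* as D_ij = P_j + W_ij. P_j is the practice value and W_ij the patient's departure from it. Let δ be the mean of W among SMI patients minus the mean of W among controls in the same practice. Practice-level IMD is a function of *j* alone.

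- Within a matched set all members share *j*, so the contrast in practice IMD is P_j − P_j = 0.
- The contrast in actual deprivation is (P_j − P_j) + δ = δ.
- Conditioning on P_j, or on its quintile, leaves δ as it was.

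This holds for any values of P and δ. The only thing that practice IMD can change is an imbalance in P_j between the groups, which arises if the number of controls per case varies across practices.

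**Step 2: illustrative simulation.** All effect sizes are assumptions. There were 700 practices, a continuous outcome, a true SMI effect of 0, SMI patients 0.5 SD more deprived within practice, and a deprivation effect of 1 per SD. The full within-practice bias is therefore 0.5 × 1 = 0.5. With a fixed ratio of 1:4 the SMI estimates were:

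| Between-practice share of deprivation variance | Unadjusted | Adjusted, practice quintile | Adjusted, patient quintile |
|---|---|---|---|
| 0 | 0.5006 | 0.5006 | 0.0541 |
| 0.1 | 0.4857 | 0.4857 | 0.0359 |
| 0.3 | 0.4980 | 0.4980 | 0.0474 |
| 0.5 | 0.5031 | 0.5031 | 0.0597 |

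Practice quintile removes 0% of the bias. Patient quintile removes between 1 − 0.0597/0.5031 = 88% and 1 − 0.0359/0.4857 = 93%. That is a best case, because the simulated quintile is cut from the very deprivation that drives the outcome; an area-of-residence index would remove less.

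With one to four controls per case in the less deprived practices and four elsewhere (between-practice share 0.3), adjustment for practice quintile moved the estimate from 0.41 to 0.50. It corrected the between-practice imbalance and left the whole within-practice bias of 0.5.

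**Step 3: possible size on the CVD relative risk.** For a binary deprivation indicator with prevalence p1 in SMI patients and p0 in controls of the same practice, and relative risk R for CVD, the bias factor is [1 + (R − 1)p1] / [1 + (R − 1)p0]. The documents give none of these inputs, so the values are assumed.

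| p1 | p0 | R | Bias factor |
|---|---|---|---|
| 0.30 | 0.25 | 1.3 | 1.09 / 1.075 = 1.014 |
| 0.40 | 0.25 | 1.5 | 1.20 / 1.125 = 1.067 |
| 0.40 | 0.25 | 2.0 | 1.40 / 1.25 = 1.12 |

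At the upper end, an observed 1.3 would correspond to 1.3 / 1.12 = 1.16. At the lower end the effect is negligible. The formula applies only where SES acts as a confounder.

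**The case against.** Several arguments limit the point, and most of them stand.

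- *SES is not a confounder in the plan's own DAG for objective 1.* Correct. A reader might infer that the main weight-change estimate is biased by missing SES adjustment. The documents do not support that: SES is on an indirect path, and adjusting for it would block part of the total effect. For the other objectives the DAGs are in a supplement that was not available, so the role of SES there cannot be settled. The Discussion nonetheless treats poverty as a confounder, and that is the claim at issue.
- *IMD has a small stated role.* Data linkage confines it to description and secondary analyses. But Table 2 lists SES among the covariates for the fully adjusted models, so the role is not only descriptive.
- *The estimate may move.* A reader might infer that baseline SES will be exactly balanced and that adjustment will change nothing. That follows only with a fixed ratio. The plan allows up to four controls, speaks of frequency matching, and states no analysis conditional on matched sets. The variable-ratio simulation shows movement, but no within-practice correction.
- *An interaction with practice IMD is a legitimate question.* It is, if reported as effect modification by practice or area deprivation. Only presenting it as patient-level SES would be wrong.
- *The magnitude is assumed.* True. A reader might take 1.12 as a demonstrated bias; nothing in the documents establishes it.
- *The Discussion may state the real intention.* Possibly. In that case the statistical consequence disappears, and only Data linkage and the Table 2 footnote need correcting.

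**Conclusion.** The contradiction is certain from the text: practice level in Data linkage and Table 2, patient level in the Discussion. If the Methods govern, it is equally certain that the covariate cannot adjust for within-practice deprivation differences, because that follows from matching on practice and not from any assumed effect size. The fully adjusted and secondary models, the baseline SES comparison and the SES interaction then cannot bear the reading that the Discussion gives them.

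The objective 1 total-effect model and the sample size are unaffected. How much bias remains elsewhere is unknown. The range of 1.01 to 1.12 rests wholly on assumed prevalences and relative risks and on SES being a confounder for the outcome concerned. The point deserves correction before analysis, but it does not undermine the study as a whole.

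**What to change.** State one level of IMD throughout.

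- *Preferred:* in Data linkage and the Table 2 footnote, specify IMD linked to the patient's area of residence, as the Discussion already says. Use it in the baseline table, the fully adjusted and secondary models, and the SES interaction. Keep SES out of total-effect models wherever the DAG treats it as a mediator, and reconcile the Discussion's description of poverty as a confounder with that DAG.
- *If only practice-level IMD can be obtained:* correct the Discussion, state that within-practice deprivation is uncontrolled, and label every SES result as practice- or area-level.

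The first option costs a patient-level linkage request and some patients with missing linkage, though the cohort is already restricted to patients eligible for linkage. It remains an area proxy and would reduce, not remove, confounding by individual poverty. The second option costs only wording, but gives up the claim that poverty has been addressed.
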